# The effectiveness of blended versus regular Forensic Outpatient Systemic Therapy in the treatment of juvenile antisocial behavior: a study protocol of a randomized controlled trial

**DOI:** 10.1186/s12888-023-04831-8

**Published:** 2023-05-04

**Keywords:** Effectiveness, Randomized controlled trial, Forensic Outpatient Systemic Therapy (FAST), Antisocial behavior, Delinquency, Recidivism, Blended care

## Abstract

**Background:**

Antisocial behavior during adolescence can have long-lasting negative effects and leads to high societal costs. Forensic Outpatient Systemic Therapy (Forensische Ambulante Systeem Therapie; FAST) is a promising treatment for juveniles aged 12–21 showing severe antisocial behavior. The intensity, content and duration of FAST can be adjusted to the needs of the juvenile and their caregiver(s), which is considered crucial for effective treatment. Next to the regular version of FAST (FASTr), a blended version (FASTb) in which face-to-face contacts are replaced by minimally 50% online contacts over the duration of intervention was developed during the Covid-19 pandemic. The current study will investigate whether FASTb is equally effective as FASTr, and through which mechanisms of change, for whom, and under which conditions FASTr and FASTb work.

**Methods:**

A randomized controlled trial (RCT) will be carried out. Participants (*N* = 200) will be randomly assigned to FASTb (*n* = 100) or FASTr (*n* = 100). Data collection will consist of self-report questionnaires and case file analysis, and include a pre-test at the start of the intervention, a post-test immediately after the intervention, and a six month follow-up. Mechanisms of change will be investigated using monthly questionnaires of key variables during treatment. Official recidivism data will be collected at two-year follow-up.

**Discussion:**

This study aims to improve the effectiveness and quality of forensic mental health care for juveniles with antisocial behavior by studying the effectiveness of blended care, which has not been studied before in treatment of externalizing behavior. If found to be at least as effective as face-to-face treatment, blended treatment can help meet the urgent need for more flexible and efficient interventions in this field. In addition, the proposed study aims to unravel what works for whom, knowledge urgently needed in mental health care for juveniles with severe antisocial behavior.

**Trial registration:**

This trial was registered at ClinicalTrials.gov on 07/11/2022, registration number NCT05606978.

**Supplementary Information:**

The online version contains supplementary material available at 10.1186/s12888-023-04831-8.

## Background

Juvenile antisocial behavior, resulting in delinquent acts such as threatening, assault, property crime, and substance and weapon offences [1], can have long-lasting and devastating effects such as out of home-placement, recidivism, and delinquency during adulthood [2]. In addition, these juveniles have an increased risk of substance abuse and a criminal lifestyle during adulthood [3], and are less likely to have stable living situations, relationships, and work environments [4]. Juveniles with antisocial behavior negatively affect societal safety and induce high societal costs [5]. Considering the long-lasting personal and societal consequences of juvenile antisocial behavior [3–5], evidence-based treatment is vital for not only the juveniles and their systems, but also for society. However, juveniles with antisocial behavior are hard to reach and motivate for treatment. Prompted by the recent Covid-19 pandemic, the question rose whether interventions can be offered partially online, as this increases accessibility and potentially helps to involve these juveniles in treatment. The current protocol paper describes a randomized controlled trial (RCT) aiming to compare the effectiveness of blended versus regular Forensic Outpatient Systemic Therapy (Forensische Ambulante Systeem Therapie; FAST) [6], targeting severe antisocial behavior in juveniles.

### FAST

FAST is an outpatient systemic intervention for juveniles (aged 12–21 years) who show antisocial behavior and their multi problem families. The primary aims of FAST are to (1) reduce juvenile antisocial and/or delinquent behavior; (2) prevent out of home placement; and (3) prevent or decrease recidivism (risk) [6]. The secondary goals of FAST are to reduce substance use and contact with deviant peers, and to reach client formulated goals. FAST is based on the socio-ecological model by Bronfenbrenner [7] and addresses relevant systemic, family, and child factors using components that originate from cognitive behavioral therapy, system therapy, non-violent resistance and aggression regulation therapy.

FAST can be distinguished from other systemic interventions targeting antisocial behavior in juveniles by being especially adherent to the Risk Needs Responsivity (RNR) principles by Andrews and Bonta [8]. The RNR model is a leading and empirically well-substantiated model in criminology, and specifies that interventions should adhere to three principles in order to be effective: (1) the risk principle: non-intensive interventions should be offered to low recidivism risk clients, and high-intensive intervention should be offered to high recidivism risk clients; (2) the need principle: interventions should target the dynamic individual criminogenic needs during treatment; and (3) the responsivity principle: interventions should be responsive to the abilities of the client (system). FAST is very flexible in adhering to the RNR principles. FAST can be offered longer lasting and more intensive if needed, it addresses criminogenic risk and protective factors within the broad social context of a client system, and it is responsive to the abilities of the client system. Furthermore, FAST can be combined with other treatments to address the specific individual risk factors of a client (system). For instance, the intervention may combine individual therapy for caregivers with stress reduction or trauma therapy for juveniles.

FAST is a promising intervention targeting juveniles with antisocial behavior and their families [6]. Preliminary findings from pretest-posttest studies suggested that FAST resulted in some promising positive changes on the desired outcomes: FAST had a large effect in reducing general recidivism risk, a moderate effect in decreasing problems in the emotional/personal functioning of the juvenile, and a small to moderate effect in improving family functioning [9]. Additionally, FAST has been found to have sufficient program integrity [10], which is important as treatment integrity is generally associated with a higher treatment effectiveness [11]. However, more robust studies are needed to substantiate these results.

### Blended care: FAST blended (FASTb)

Prompted by the worldwide Covid-19 pandemic, a blended version of FAST has been developed (FASTb). Content wise, FASTb is nearly identical to regular FAST (FASTr). However, FASTb offers a combination of face-to-face and online treatment, consisting of a minimum average of 50% online direct treatment time over the duration of the intervention (such as phone calls, video calls, text messages, and eHealth; for more information, see Conditions). Blended interventions have several benefits over sole face-to-face intervention [12]. They increase accessibility and allow clients to work on therapy at any given moment, allow for precise registration of treatment delivery, increase (online) access to training materials for clients, involve lower time commitment for clinicians, and involve lower costs [13]. Moreover, blended interventions might be especially beneficial in the treatment of juveniles with antisocial behavior, as these interventions are expected to be even more flexible in adhering to the RNR principles than sole face-to-face treatment [14]. Blended intervention is less dependent on time and place, which increases the flexibility and accessibility of the intervention. It fits the increased use of the internet by juveniles and can be more responsive to the individual learning style or preference by offering both reading and visual material. Thereby, blended intervention might help reaching more clients and increase the involvement of this hard-to-reach target group in treatment. In fact, the integration of technological platforms in interventions has been employed to better reach juveniles and their families [15].

Despite these possible benefits, therapist implementation of blended interventions in forensic mental health care has been found to be disappointing, even though therapists viewed blended interventions as having potential to improve treatment quality [16]. The study of Kip et al. [17] investigated what could increase therapist use of blended interventions in forensic mental health care. Therapists indicated a need for more technological knowledge and highlighted the importance of the basic technological prerequisites, such as a stable internet connection. Further, they voiced that more research should be conducted to determine the actual effectiveness of blended interventions in the forensic field, and to specifically focus on why and for whom blended interventions work.

Unfortunately, to our knowledge, no research has investigated the effectiveness of blended interventions targeting juvenile externalizing behavior in general, let alone antisocial behavior or the complex and comorbid problems present in forensic youth care. Based on studies conducted on the effectiveness of blended intervention targeting several internalizing psychopathologies in juveniles, such as depression and anxiety, it can be concluded that blended treatment seems equally effective as face-to-face treatment. Previous research found blended interventions for depression and anxiety to be more effective than no intervention [18, 19] and active control groups [18], and equally effective as face-to-face interventions [20]. Further, a review showed that blended interventions aiming to reduce adult substance use were associated with lower dropout rates and greater abstinence than face-to-face interventions [12]. To determine if blended therapy is as effective as face-to-face therapy for juveniles with antisocial behavior, the current study is the first to investigate a blended intervention targeting juveniles with antisocial behavior by comparing the effectiveness of FASTb and FASTr.

### Mechanisms of change

According to the program theory [6], FAST aims to reach its primary and secondary goals by targeting risk factors at the level of the individual, the family, and the broader system of the juvenile. At the individual level, FAST targets criminogenic needs of the juvenile related to psychological functioning – such as cognitive distortions [21, 22]. At the family level, FAST is directed at improving caregiver-child relationship quality, caregiver behavior, and caregiver competence, and reducing conflicts between caregivers and juveniles [23, 24]. At the level of the broader system of the juvenile, FAST aims to target systemic risk factors by promoting social support [25], reducing interaction with deviant peers [26, 27], and decreasing truancy [28]. The current study will investigate whether the hypothesized mechanisms of change (social support, family functioning, and cognitive distortions) indeed contribute to the effectiveness of FASTb and FASTr.

### Moderators: what works for whom?

Intervention research continues to emphasize the importance of identifying subgroups for which and conditions under which interventions work best. Despite, there is still a lack of knowledge on what works for whom and under which conditions within interventions targeting antisocial and delinquent behavior of juveniles [29]. As such, the current study will investigate the influence of various moderators. Regarding treatment conditions, assessing program integrity (i.e., whether FAST is implemented as originally protocolled) is key, as non-significant or negative results may be caused by incorrect program implementation rather than an ineffective program [30]. Indeed, previous research has shown that treatment effectiveness in interventions targeting juvenile antisocial behavior is higher with higher treatment integrity [30–32], as well as stronger therapist-client alliance [33], higher treatment expectancies [34], and more social support [25]. Several studies have shown intervention effectiveness to also be higher with higher treatment cooperation [35], treatment motivation [36], and therapist experience [37], but these moderators have not yet been investigated for interventions targeting juvenile antisocial behavior. Further, demographic variables, such as gender [37], age, cultural background, and problem severity also influence treatment effectiveness [38]. By studying these moderating factors, we aim to determine which juveniles and families benefit most from FASTb and FASTr, and under which conditions.

### Aims of the study

The current study protocol describes an RCT comparing the effectiveness of FASTb and FASTr in the treatment of juveniles with antisocial behavior and their families. In addition, we will investigate the mechanisms of change of FASTb and FASTr, and for whom and under which conditions FASTb and FASTr work best. Thereby, new innovative steps will be taken to possibly improve the effectiveness and quality of mental health care for juveniles with antisocial behavior.

To this end, the aims of this study are threefold. The first aim is to compare the effectiveness of FASTb and FASTr in terms of reducing externalizing behavior, delinquency, out of home placement, and recidivism (risk) (primary treatment goals), and in terms of reducing substance use, contact with deviant peers, and in reaching client formulated goals (secondary treatment goals). It is expected that FASTb and FASTr are equally effective in reaching the primary and secondary goals of FAST. The second aim is to identify potential mechanisms of change in FASTb and FASTr. It will be investigated whether FASTb and FASTr, conform program theory, positively affect the intermediate outcomes: social support, family functioning (i.e., caregiver-juvenile conflict, caregiver-juvenile relationship quality, caregiver behavior, and caregiver competence), and cognitive distortions [6]. It is expected that these factors mediate the effectiveness of FASTb and FASTr. The third aim is to investigate what program and participant characteristics moderate FASTb and FASTr effectiveness. In other words, we aim to determine which families benefit most from FASTb and FASTr, and under which conditions. It is expected that the effectiveness of FASTb and FASTr is moderated by client factors (demographics such as gender and age, juvenile and caregiver psychopathology, and social support) and treatment characteristics (treatment integrity, treatment duration, intensity and completion, therapist-client alliance, motivation, expectancies, and cooperation). See Fig. 1 for a conceptual model of the research design.

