#### Sample size calculation

Based on a MANOVA a priori power analysis, a group of *n* = 120 (*n* = 60 per group) will allow us to identify – with a power of 0.80, an alpha of 0.05 – small differences (d = 0.15) in effectiveness between FASTb and FASTr (G*power 3.1) [40]. To account for possible drop-out, which was approximately 20% in our previous comparable study [41], *n* = 200 participants will be recruited. Based on the number of juveniles referred to FAST at the treatment sites participating in this project (approximately 120 juveniles yearly), and participation rates of 70–90% in our earlier comparable studies [41, 42], it is considered feasible to include in total *n* = 200 juveniles and their caregivers within three years.

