#### Effectiveness

Research questions related to the effectiveness of FASTb versus FASTr on the primary and secondary outcomes will be answered using co-variance analyses with a correction for multiple testing, with the pre-test (T1) score on the dependent variable as a covariate, the post-test (T2) and 6-month follow-up (T3) scores as the dependent variable, and the condition (FASTb or FASTr) as a factor. Dichotomous outcome variables will be tested with Chi-square analysis to compare the percentage of the FASTb and FASTr conditions. Recidivism data after two years (T4) will be analyzed using Kaplan Meyer and Cox survival analyses. Effect sizes will be computed as Cohen’s d, based on adjusted means and standard errors.

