## Discussion

This study protocol describes an RCT comparing the effectiveness of FASTb and FASTr in the treatment of juveniles with antisocial behavior and their families. In addition, we will investigate the mechanisms of change of FASTb and FASTr, and for whom and under which conditions FASTb and FASTr work best. The hypotheses are that (1) FASTb and FASTr are equally effective in reaching the primary and secondary goals of FAST; (2) conform program theory, social support, family functioning, and juvenile cognitive distortions mediate effectiveness of FASTb and FASTr; and (3) the effectiveness of FASTb and FASTr is moderated by demographics, juvenile and caregiver psychopathology, social support, and treatment characteristics.

In the past years, blended mental health care has increased due to the need for time-efficient and cost-effective interventions, the development of digital tools, and the further digitization of society [64]. Blended treatment has several benefits over sole face-to-face therapy such as increased accessibility, lower time commitment for clinicians, and lower costs [12]. Moreover, for juveniles with antisocial behavior, blended treatment might be even more beneficial as it lends itself to be even more flexible in adhering to the RNR principles than sole face-to-face treatment. Although blended treatment has been shown to be effective in several studies investigating internalizing problems [12, 18, 20], this study will be the first to investigate the effectiveness of blended treatment for juveniles with antisocial behavior. Thereby, this study aims to improve the effectiveness and quality of forensic mental health care for these juveniles.

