## Conclusion

The present study aims to compare the effectiveness, mechanisms of change, and moderators of FASTb and FASTr. Evidence-based treatment is vital for not only juveniles with antisocial behavior and their systems, but also for society. If found to be at least as effective as face-to-face treatment, blended treatment can help meet the urgent need for more flexible and efficient interventions in juvenile justice context. The results of this study are of importance to all countries that aim to treat juveniles with antisocial behavior effectively and efficiently.

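### The aim is equal (or at least equal) effectiveness, but the trial is sized and tested for a difference, with no criterion for concluding equality

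*Protocol article*

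**What the plan says.** Every statement of the aim in the Protocol article is about equality or non-inferiority:

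- Abstract, Background: "The current study will investigate whether FASTb is equally effective as FASTr".
- Aims of the study: "It is expected that FASTb and FASTr are equally effective in reaching the primary and secondary goals of FAST". The Discussion repeats this as hypothesis (1).
- Conclusion: "If found to be at least as effective as face-to-face treatment", blended treatment is put forward as an answer to a service need. The Discussion part of the Abstract uses the same condition.

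The statistical sections follow a different logic. Sample size calculation describes a MANOVA-based calculation "with a power of 0.80, an alpha of 0.05" for identifying "small differences (d = 0.15) in effectiveness between FASTb and FASTr". Under Effectiveness, the questions on primary and secondary outcomes "will be answered using co-variance analyses with a correction for multiple testing", with condition as the factor and the T1 score as covariate. Dichotomous outcomes get a chi-square test, two-year recidivism gets Kaplan-Meier and Cox analyses, and effect sizes are reported as Cohen's d. Plan of data analysis adds an intention-to-treat set, imputation and a completers-only analysis. Nothing in the article gives a margin, an interval rule or any other statement of which result would count as equally or at least as effective.

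**The concern.** Each of the named tests takes no difference as its null hypothesis. Failing to reject that null shows only that the data did not distinguish the arms, which can happen because the arms are alike or because the estimate is imprecise. The error that matters for this aim is concluding equality when FASTb is worse, and the plan does not control it. The multiplicity correction guards against falsely declaring a difference. In a trial that hopes to find none, it makes a non-significant result more likely.

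Equal and at least as effective are also different claims. The first needs both sides of the interval bounded, the second only one, and the article uses both. At stake is the main conclusion, which the article links to wider use of blended care in a juvenile justice setting.

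**Working it through.** **The plan's own figure.** Sample size calculation gives 60 per group for d = 0.15, alpha 0.05 and power 0.80. For a two-group comparison of means, n per arm = 2(1.96 + 0.84)²/d² = 2 × 7.85/0.0225, about 698. At 60 per arm the power for d = 0.15 is about 13%. The 120 was not reproduced in MANOVA or repeated-measures settings with 0.15 read as d. A total near 120 appears only if 0.15 is another metric (for example f = 0.15, three waves, zero correlation: 119). That is a separate matter. What counts here is that the calculation is for detecting a difference, and that 0.15 is the difference to detect, not a margin.

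**Inputs for the check.**
- n = 80 per arm: 200 × (1 − 0.20)/2, using the article's target and its drop-out figure.
- Two-sided alpha 0.05: the article gives 0.05 without sidedness.
- Correlation r between T1 and outcome: not given; assumed 0 to 0.6.
- Standard error of the adjusted difference in SD units: SE = √(2(1 − r²)/n). At r = 0: √(2/80) = 0.158. At r = 0.6: √(2 × 0.64/80) = 0.126.

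**Chance that a real difference is non-significant (non-central t).**

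| True d | r = 0 | r = 0.6 |
|---|---|---|
| 0.15 | 84% | 78% |
| 0.30 | 53% | 35% |
| 0.50 | 12% | 2.5% |

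Rough check for d = 0.30: Φ(1.96 − 0.30/0.158) = Φ(0.06), about 52%; Φ(1.96 − 0.30/0.126) = Φ(−0.41), about 34%.

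The article does not name the correction. As an illustration, take Bonferroni over the seven primary ANCOVAs (YSR, CBCL and SDB at T2 and T3, recidivism risk at T2). The d = 0.30 figures then become 79% (r = 0) and 63% (r = 0.6).

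**What a null result leaves open.** The 95% half-width is 1.96 × SE: 1.96 × 0.158 = 0.31 (r = 0) and 1.96 × 0.126 = 0.25 (r = 0.6). With r = 0.6, an observed difference of 0.20 SD against FASTb would be non-significant, yet its interval would run from about −0.05 to 0.45.

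**What a non-inferiority rule could deliver.** With no true difference, power = Φ(margin/SE − 1.96). The margins are assumed, since the article gives none.

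| Margin (SD) | r = 0.5 (SE 0.137) | r = 0.6 (SE 0.126) |
|---|---|---|
| 0.30 | 59% | 66% |
| 0.35 | 72% | 79% |
| 0.40 | 83% | 89% |

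These are for one outcome. Counting YSR, CBCL and SDB at T2 and T3 (6), recidivism risk at T2 (1), placement at T2 and T3 (2) and convictions (1) gives 10 primary tests. If all 10 had to meet a 0.40 margin with the per-test power above, joint power would be 0.83¹⁰ to 0.89¹⁰, or 16% to 31%, if independent. With an assumed correlation of 0.5 between tests it would be about 44% to 57%.

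**The case against.** The strongest reply is that the aim is worded as comparing effectiveness, with equality only an expectation. The article never calls itself an equivalence or non-inferiority trial, and a margin could sit in a full protocol or analysis plan that is not shown. The last point has force: a missing margin alone would not be a finding against a condensed article. The mismatch remains, because the article does print the hypothesis, the sample-size basis and the tests, and they do not fit together. A margin would also drive the sample size, and the printed calculation uses none.

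Three stronger readings are tempting and are not supported.

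- A reader might infer that the investigators will take a non-significant result as proof of equality. No passage says so, and effect sizes are to be reported. The article simply offers no other route to its hypothesis.
- A reader might infer that a clearly worse FASTb would pass as equal. A true d of 0.50 is missed only 2.5% to 12% of the time at 0.05. The exposure is to small and small-to-moderate differences.
- A reader might infer that equivalence within 0.15 could never be shown. The 90% half-width at 80 per arm is 0.19 (r = 0.7) to 0.26 (r = 0). At 100 per arm with r = 0.8 it is 1.645 × √(2 × 0.36/100) = 0.14, and 0.15 is not stated as a margin anyway.

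Nor is it fair to say that drop-out and blurring of the arms go unaddressed. Intention-to-treat analysis, imputation and a completers set are planned. The online share is measured in two ways, calculated every three months, and belongs to the treatment characteristics tested as moderators. These are real safeguards, but none supplies a criterion for equality.

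**Conclusion.** The point stands as an internal mismatch. The article asks whether FASTb is equally, or at least as, effective, but sizes and tests for a difference, so the analysis as written cannot deliver its main conclusion. Under the assumptions of 80 analysed per arm, two-sided 0.05 and T1 correlation 0 to 0.6, a moderate shortfall of d = 0.30 goes undetected between about a third and half of the time before any multiplicity correction. A null result leaves differences of up to roughly 0.25 to 0.31 SD open around a zero estimate. The size depends on the correlation, the number analysed and the correction chosen, none of which the article fixes. The logical gap does not depend on them. It should be settled before any outcome analysis, since a margin set after seeing results carries little weight.

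**What to change.** 1. Choose one framework before any outcome analysis. Non-inferiority of FASTb fits the wording of the Conclusion and of the Abstract's Discussion.
2. Name one or a few key primary outcomes and justify a margin on each outcome's own scale: a mean difference for continuous outcomes, a risk difference for placement, a hazard ratio for convictions.
3. Conclude only if the confidence interval of the adjusted difference lies within the margin (two-sided 95% for non-inferiority, 90% for equivalence by two one-sided tests at 0.05). Otherwise report the result as inconclusive.
4. Report this in the intention-to-treat set. Repeat it as a sensitivity analysis in families who received the online share of their assigned arm (at least 50% in FASTb, at most 10% in FASTr), which Treatment characteristics already measures. The completers-only set does not select on this.
5. If no margin can be justified, reword the aim and conclusion as estimating the difference with its confidence interval, and do not claim equal effectiveness from non-significance.

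The cost is agreement on margins and a change to the analysis plan and registration; no new measurements are needed. The price is that the trial may end inconclusive. Single-outcome non-inferiority power is about 59% to 66% at a margin of 0.30 SD and 83% to 89% at 0.40, and much lower if every primary outcome must meet its margin. That is the reason to keep the key outcomes few.
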